#### Informed Consent and Confidentiality

Informed consent is a process that will begin with IRB review of all recruitment materials. All study personnel will complete mandatory training in the protection of human subjects in research, including the courses of study contained in the Collaborative Institutional Training Initiative program [108], as required by the IRBs of Nova Southeastern University and Emory University, and only trained personnel will be involved in the process. The informed consent process will continue as study personnel explain study procedures during the education process preceding the request for written informed consent.

Participants will be protected from the risk of inadvertent disclosure of their health status or other health-related information by identifying all study-related data collection instruments by the participant's study number. Participants' identities will only be linked to data via a list that includes participant names and contact information and their participant identification number. All study databases will be kept on password-protected computers or secure servers (REDCap). Paper copies of all materials will be kept in locked filing cabinets in the investigators’ offices.

### Institutional Review Board Approval

Phase 1 (qualitative) study procedures were approved by the IRBs of Nova Southeastern University and Emory University. Phase 2 (clinical trial) study procedures have received preliminary approval by the IRBs of Nova Southeastern University and Emory University. Final approval is pending development and board review of actual intervention materials prior to their use with participants. Written informed consent will be obtained from all participants.

### Data Analyses

#### Initial Data Management

Initial review will evaluate data for completeness and valid characteristics through inspection of descriptive statistics. Although every effort will be made to minimize loss to follow-up, we recognize that some attrition is likely to occur. We will evaluate patterns of missingness in the data and follow widely-recommended procedures for dealing with this issue [109]. If our evaluation shows that missing data can be considered as missing at random (MAR) then our use of full-information maximum likelihood routines in MPlus statistical software (Muthén & Muthén; Los Angeles, California) will result in unbiased estimates of parameters [110]. If data are not MAR, we will include pattern of missingness in random effects pattern mixture analyses [111]. Group equivalence on demographic characteristics (except those defining group membership) and baseline measures not used in assignment will be assessed, and if differences are found these variables will be used as covariates in analyses. Other analyses will evaluate the distributional properties of dependent variables to assess the suitability of planned statistical models.

#### Study Hypotheses

Hypotheses will be tested via three aims, detailed below.

##### Aim 1

*Hypothesis 1* regarding the sensitivity of alternate forms of the health literacy measure to the intervention will be tested by calculating the simple sum of the HL and NUM scales for baseline (Form A) and first follow-up (Form B), and test their difference via paired *t*-tests, since this is a straightforward strategy that might be used in research and clinical work. This hypothesis will also be evaluated using a mixed-effects regression model with repeated measures for all three assessments that will include relevant covariates such as race/ethnicity, age, education, and cognition. Models for completers and intent-to-treat groups will be created. *Hypothesis 2*, regarding the validity of the measure on tablet computers, will be assessed by evaluating item difficulties and discriminations, calculation of scales’ internal reliabilities (Cronbach alpha), evaluation of construct validity via examination of the measure’s factor structure, and evaluation of concurrent validity as correlations and partial correlations of FLIGHT/VIDAS scales with other measures (Test of Functional Health Literacy in Adults, REALM, and SAHLSA). Measures of scale characteristics (mean, standard deviation, Cronbach alpha, and correlations with other measures) will be compared to values obtained for the full-size computer administration obtained during an earlier study [25] using tests for differences in means, standard deviations, and correlations.

##### Aim 2

*Hypotheses 3* and *4* for this aim, related to the effects of the intervention on outcomes, will also be evaluated in mixed-effects regression models including relevant covariates, with separate models assessing each dependent variable (HL and NUM scales, SF-36 General Health, Chronic Disease Self-Efficacy Scale, Patient Activation Measure, and treatment adherence) providing the ability to evaluate between-groups differences and the interaction of group membership (each racial/ethnic group). Estimated marginal means for mixed-effects models will be compared across levels of effects. Exploratory analyses will evaluate the effect of the intervention on other outcomes, such as patient-provider relationships, treatment engagement, and health care service utilization. Exploratory analyses will evaluate the impact of age on these outcomes. Similar analyses will evaluate the effect of the intervention on specific conditions, such as pain, sleep, and fatigue.

##### Aim 3

*Hypotheses 5* and *6* for this aim, related to the significance of effects of race, cognition, socioeconomic status, and academic skills on health status and utilities (as mediated by health literacy) will be tested using structural models developed in the MPlus statistical software. The significance of indirect (mediating) effects will be tested using bias-corrected bootstrapped estimates. *Hypothesis 6*, which suggests that levels of health literacy will moderate the effects of the intervention, will be tested by creating an interaction variable and including it in the structural model for *Hypothesis 5*.

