### Aims and Hypotheses

In Aim 1 we will adapt and evaluate the tablet computer-administered measure of health literacy developed during an earlier study with African-American, Hispanic, and white non-Hispanic individuals 40 years of age and older, which operated on tablet computers. The two hypotheses of Aim 1 are: (*Hypothesis 1*) alternate forms of the new health literacy measure’s general health literacy and numeracy scales will be sensitive to intervention effects, showing improvements after participants complete the intervention; and (*Hypothesis 2*) the new health literacy measure will be acceptable, usable, and valid when administered on tablet computers.

In Aim 2 we will use the computer-administered measure to assign participants to a racially- and ethnically-tailored intervention that is delivered in a way that is appropriate to their level of health literacy. The two hypotheses of Aim 2 are: (*Hypothesis 3*) an interactive multimedia intervention will be more effective in improving health literacy, self-reported health, patient activation, health self-efficacy, and treatment adherence compared to a matched active control intervention; and (*Hypothesis 4*) the interactive multimedia intervention tailored to participants’ characteristics will significantly reduce health literacy differences between white non-Hispanics, African-Americans, and Hispanics.

In Aim 3 we will assess mediators and moderators of the relation of health literacy to race and ethnicity. We will also explore how these mediators and moderators are linked to health behaviors and actual health outcomes. The two hypotheses of Aim 2 are: (*Hypothesis 5*) health literacy will mediate relations between age, race and ethnicity, socioeconomic status, cognition, academic skills, and health status; and (*Hypothesis 6*) health literacy will moderate response to the health literacy intervention, with blacks and Hispanics with lower initial levels showing a greater response to the intervention than white non-Hispanics with higher levels of health literacy.

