### Treatment Assignment

#### Inclusion and Exclusion Criteria

Participants will be eligible for the study if they are 40 years of age or older, are treated for at least one of the conditions in the Functional Comorbidity Index [90] (cardiovascular disease, arthritis, cancer, lung disease, osteoporosis, depression, and others) with at least one medication, have health literacy below the 8^th^ grade level as indicated by the REALM (English) or SAHLSA (Spanish), and are willing to participate for the length of the study. Potential participants will be excluded if they are not able to provide informed consent, have a cognitive or psychiatric disorder that impairs their ability to safely participate in the study, or are not able to remain involved over the full length of the study.

A screening procedure for the new project was developed by assessing the ability of the REALM [85] or SAHLSA [91] to predict if participants had an 8^th^ grade or lower level of reading on the Woodcock-Johnson or Muñoz reading tests. Using the R statistical package pROC [92], a score of 62 on the REALM predicted reading skills less than an 8^th^ grade level on the Woodcock-Johnson (area under the curve [AUC]=0.79, 95% CI 0.72-0.87; sensitivity=0.80, specificity=0.67) with similar results for the SAHLSA. Earlier analyses showed that the FLIGHT/VIDAS General Health Literacy (HL) scale will also be effective for use in detecting participants with lower levels of reading skills (all *P-* values <.001). Analyses did not differ for language groups (AUC for Spanish sample=0.86, *P*<.001).

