#### Measures

Primary outcome measures will be health literacy (FLIGHT/VIDAS), self-reported general health (Medical Outcomes Study 36-item Short Form; SF-36 [95]), health self-efficacy (Chronic Disease Self-Efficacy Scale [96]), patient activation (Patient Activation Measure [97]), and treatment adherence. Additional data will provide the ability to consider race, ethnicity, age, and other variables as potential confounders. These data will include demographic variables, mood [98], stress [99], patient-provider relationships [100], treatment engagement, general cognitive abilities, academic skills, health conditions, current symptoms, health care attitudes, self-efficacy [101], and health care utilization.

Severity and number of health conditions will be assessed with the Functional Comorbidity Index [90], a previously validated measure linked to physical status, and an index based on the Midlife in the United States study [102] protocol, as used in our earlier study [27], to allow comparisons with data from that study. Assessments will include information on the specific symptoms of key problems in chronic disease management, and will allow a pre/postevaluation of the effects of the intervention on each. Simple measures of physical status (walking speed [103], body mass index [104], and waist-hip ratio [105]) will also be obtained to assess the effects of health literacy, cognition, and comorbidity on these variables, as they have all been related to risks for mortality [6,106,107].

Most self-report instruments will be administered via Automated Computer-Assisted Self-Interview (ACASI) software with assessment materials presented on touchscreen computers. This strategy enhances data collection by allowing participants anonymity in their responses and reduces issues with hand scoring of measures and manual data entry. Both sites will use the ACASI software Questionnaire Development System (QDS; Nova Research, Bethesda, Maryland). Individually administered measures, including assessments of cognitive, academic, and health literacy status, will be hand scored and verified. QDS output files will be transferred between sites using encrypted file transfer technology also available in REDCap.

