### Expected Outcomes

Results of this study will help to establish the utility of the FLIGHT/VIDAS health literacy measure when administered on convenient tablet computers, including its validity in relation to other measures of health literacy and academic measure of reading and mathematics. Evaluation of the effects of tailoring strategies, and especially of providing information at a level appropriate for our participants’ level of health literacy, will provide a test of the usefulness of this strategy in general, and specifically as a way to test racial and ethnic disparities in knowledge and health status. Finally, mediation analyses will allow an assessment of the mediating effect of health literacy on health disparities.

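### The Hypothesis 2 validity analysis names no academic reading or mathematics criterion, though Expected Outcomes claims both, and two of its three comparators are the tests that selected the sample

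*Protocol article*

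**What the plan says.** The Expected Outcomes section says the results will help show the usefulness of FLIGHT/VIDAS on tablets, "including its validity in relation to other measures of health literacy and academic measure of reading and mathematics".

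The analysis meant to support this is in Data Analyses, Study Hypotheses, Aim 1. For Hypothesis 2 it lists item difficulties and discriminations, Cronbach alpha, factor structure, and concurrent validity as correlations and partial correlations: "correlations of FLIGHT/VIDAS scales with other measures (Test of Functional Health Literacy in Adults, REALM, and SAHLSA"). It then adds a comparison with the earlier study: "Measures of scale characteristics (mean, standard deviation, Cronbach alpha, and correlations with other measures) will be compared to values obtained for the full-size computer administration".

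Two of the named comparators are also the eligibility screen. Inclusion and Exclusion Criteria requires health literacy below the 8th "grade level as indicated by the REALM (English) or SAHLSA (Spanish").

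Academic data are collected. The Measures section lists "general cognitive abilities, academic skills, health conditions, current symptoms" among the additional data, and states: "Individually administered measures, including assessments of cognitive, academic, and health literacy status, will be hand scored and verified".

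**The concern.** The results section is told to expect a conclusion that the validity analysis does not produce. If the plan is followed as written, nobody is instructed to relate HL to an academic reading score or NUM to an academic mathematics score. NUM is the more exposed of the two: it is one of the two scales tested in Hypothesis 1 and has its own outcome model under Aim 2, yet no mathematics criterion is named for it under Hypothesis 2.

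The comparators that are named raise a second problem. Everyone enrolled has scored low on REALM or SAHLSA, so the spread of those scores is narrowed, and a narrowed spread tends to weaken a correlation. The plan sets these correlations beside values from an earlier study and tests the difference. A lower value in the tablet sample could then be attributed to the tablet when it comes from who was let in.

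**Working it through.** **Criteria claimed and criteria analysed.** The two lists compare as follows.

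| Criterion type in Expected Outcomes | Named for Hypothesis 2? |
|---|---|
| Other health-literacy measures | Yes: Test of Functional Health Literacy in Adults, REALM, SAHLSA |
| Academic reading | No |
| Academic mathematics | No |

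So 2 of the 3 claimed types are absent. Of the 3 named comparators, 3 are health-literacy tests, 2 are the entry screen and 0 are academic tests. The parenthesis carries no wording to suggest that it gives examples only.

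**Where the academic data are used.** Hypothesis 5 in Aims and Hypotheses states that "health literacy will mediate relations between age, race and ethnicity, socioeconomic status, cognition, academic skills, and health status". The Aim 3 analysis describes structural models "related to the significance of effects of race, cognition, socioeconomic status, and academic skills on health status and utilities (as mediated by health literacy"). Such a model must estimate a path from academic skills to health literacy. It is set up to test indirect effects on health status, however. It is not linked to Hypothesis 2, and it is not specified as HL against reading and NUM against mathematics.

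**Whether the earlier study was selected in the same way.** Inclusion and Exclusion Criteria says the screen was developed for the new project by asking how well REALM or SAHLSA predicted 8th-grade-or-lower reading. It reports sensitivity 0.80 and specificity 0.67 at a REALM score of 62. Specificity can only be estimated if the sample contains people who read above the threshold, so those data were not restricted by this screen. I take these data to come from the same earlier project that supplies the full-size values. The Participants section supports this by referring to data from the previous study.

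**Direction and possible size of the selection effect.** The document gives neither the unrestricted correlation nor the share screened out, so the actual effect cannot be computed. The following is an illustration only. It assumes bivariate normal scores, an unrestricted correlation r = 0.60, and direct selection of the lowest fraction p on the screening test.

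- With c the normal quantile of p and λ = φ(c)/p, the retained variance is u² = 1 − cλ − λ².
- The restricted correlation is r′ = r·u / √(1 − r² + r²u²).

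| p retained | c | λ | u² | u | r′ |
|---|---|---|---|---|---|
| 75% | 0.674 | 0.424 | 0.535 | 0.731 | 0.439/√(0.640 + 0.193) = 0.48 |
| 50% | 0 | 0.798 | 0.363 | 0.603 | 0.362/√(0.640 + 0.131) = 0.41 |
| 25% | −0.674 | 1.271 | 0.242 | 0.492 | 0.295/√(0.640 + 0.087) = 0.35 |

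Under these assumptions, selection alone takes 0.60 down to somewhere between 0.48 and 0.35 with no tablet effect at all. Correlations with tests that were not used for selection would be less affected, though not immune, because those tests are related to the screen.

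**The case against.** The strongest reply is that the academic link is not left unanalysed. A reader might infer from the Hypothesis 2 list that nothing stands behind the academic claim. The document does not support that: academic skills are measured, and the Aim 3 structural model will estimate their relation to health literacy. This stands, and it limits the point to the absence of a validity analysis of HL and NUM against the academic measures.

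A reader might also infer that support for NUM rests mainly on reading tests. That is not shown. The document uses REALM and SAHLSA as reading screens, but it does not describe the content of the third test. Hypothesis 2 also relies on item statistics, reliability, factor structure and comparison with the full-size version, and the measure is reported as already validated in the earlier study.

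Expected Outcomes is a narrative paragraph that says results will help to establish utility, and Hypothesis 2 itself names no academic criterion. The article also condenses a fuller plan. These arguments lower the weight of the point but do not remove it, because the article gives what reads as a closed list and then claims something outside it.

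Finally, selection on the screen would more likely understate validity than create false support for it. That is correct for the correlations alone. It does not answer the planned test against the earlier values, where an understated correlation is the result that could mislead.

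**Conclusion.** The point holds as a minor inconsistency with a free improvement. Two of the three criterion types claimed under Expected Outcomes have no counterpart in the Hypothesis 2 validity analysis. The REALM and SAHLSA correlations come from a sample selected on those tests, yet are to be compared with a study that was not selected by this screen. The direction of the selection effect is clear, but its size is unknown.

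This rests on two assumptions: that the academic battery contains both a reading and a mathematics measure, as Expected Outcomes implies, and that the screening data and the full-size comparison values come from the same unscreened project.

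Nothing here touches the randomised comparison: Hypotheses 3 and 4, their models and the sample size are unaffected.

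**What to change.** Either of two routes resolves the mismatch.

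1. In the Hypothesis 2 analysis, add correlations and partial correlations of HL with the academic reading measure and of NUM with the academic mathematics measure, by language.
2. Otherwise, remove the academic reading and mathematics claim from Expected Outcomes.

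In either case, state under Hypothesis 2 that the REALM and SAHLSA correlations, and their comparison with the earlier study, are affected by range restriction and will be corrected or interpreted accordingly. A standard correction needs the ratio U of the REALM or SAHLSA standard deviation in the earlier sample to that in the enrolled sample: r = r′U / √(1 − r′² + r′²U²), assuming linearity and constant residual variance. The sponsor should be able to obtain both standard deviations, since the earlier scores were used to derive the cut-off.

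The cost is a few extra correlations and one or two sentences. No new measure, visit or participant is needed.

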#### Participants

We will recruit Spanish- and English-speaking persons aged 40 years and older whose health literacy is at the 8^th^ grade level or lower. Literacy levels will be assessed via validated scores on the Rapid Estimate of Adult Literacy in Medicine (REALM) [85], or the Short Assessment of Health Literacy in Spanish Speaking Adults (SAHLSA) [86]. This level was chosen to include persons in the lower end of the basic proficiency level and below, as defined by the US National Assessment of Adult Literacy [1,87-89]. The REALM and SAHLSA were selected based on their demonstrated relation to health status in other studies and data from our previous study that enabled us to use them as screening tools. The intervention will thus target those most likely to profit from instruction at a moderate difficulty level approximately two grade levels lower than this (6^th^ grade), or those who may need low-literacy level instruction (3^rd^ grade) based on their instructional reading level being approximately two grade equivalents below the tested level. English-speaking participants will include approximately equal numbers of African-Americans and non-Hispanic whites, with recruitment stratified by age decades (to enhance existing FLIGHT/VIDAS norms) from age 40, with no upper limit. Considering the importance of broadening the geographic basis of our normative population and ensuring the usefulness of the health literacy intervention for diverse groups, in the proposed study we will expand data collection to include Grady Memorial Hospital in cooperation with our collaborators at the Morehouse School of Medicine and Emory University (all in Atlanta, Georgia). We will continue to recruit African-American, white non-Hispanic and Hispanic participants at our Nova Southeastern University site, as we did in our earlier project. During this project, we plan to expand our recruiting efforts in South Florida to include larger numbers of Spanish speakers with low educational backgrounds who are originally from Mexico. We will randomize 432 participants, as needed (216 at each site; see power analyses for sample size justification, below). Numbers of participants in Figure 1 reflect planned recruitment based on power analysis and potential attrition.

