#### Recruitment and Retention

Recruitment at the Atlanta sites will take place in the Primary Care clinics of Grady Health Services and Emory Healthcare. Grady Health Services is the largest public health provider in Georgia, and fifth largest in the nation, with more than 130,000 outpatient visits per year. Emory Healthcare has satellite clinics throughout metro-Atlanta and serves a broad array of patient demographics and backgrounds. In current studies, it is possible to access the electronic medical record to prescreen study participants. We will continue this practice after obtaining Institutional Review Board (IRB) permission. The study recruiter will identify potential participants meeting inclusion criteria; he or she will then meet with clinic staff and providers, supply them with study information (flyers, brochures), and ask the clinic staff/provider to give the study information to these potential participants. Passive recruitment through study flyers and information about the study on clinic phone-wait systems will also be used. All studies utilizing these procedures are currently on target with recruitment goals.

In addition to a pool of subjects who participated in prior studies and have given permission to contact them in future studies, Spanish-speaking Hispanics will be recruited from Nova Southeastern University internal, family, and geriatric medicine clinics. Special efforts will be made to recruit a diverse group of Hispanics representative of South Florida and the rest of country’s Hispanic population, per US census data, particularly with respect to country of reference and educational attainment. In our previous study, we recruited more than 320 Spanish-speaking Hispanics over 3 years of active recruitment [25-28].

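### Hypothesis 2 compares the tablet scale in low readers with values from an earlier sample that included higher readers, so device and selection cannot be told apart

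*Protocol article*

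**What the plan says.** The comparison is in the protocol article under Data Analyses, Study Hypotheses, Aim 1. The quantities at issue are given there as "Measures of scale characteristics (mean, standard deviation, Cronbach alpha, and correlations with other measures"). For the tablet version, the plan is that these "will be compared to values obtained for the full-size computer administration obtained during an earlier study [25] using tests for differences in means"; SDs and correlations are to be tested in the same way. Alpha is among the quantities compared, but no test is named for it. The same paragraph lists other evidence for Hypothesis 2: item difficulties and discriminations, internal reliability, factor structure, and "evaluation of concurrent validity as correlations and partial correlations of FLIGHT/VIDAS scales with other measures", namely the Test of Functional Health Literacy in Adults, the REALM and the SAHLSA.

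Who supplies the tablet data is set under Phase 2, Participants, where entry is capped at 8th grade: "We will recruit Spanish- and English-speaking persons aged 40 years and older whose health literacy is at the" (the sentence goes on to name that cap). The inclusion criteria require that participants "have health literacy below the 8^th^ grade level as indicated by the REALM (English) or SAHLSA (Spanish"). The REALM and SAHLSA were chosen partly because of "data from our previous study that enabled us to use them as screening tools". The inclusion section then gives, for a REALM score of 62 against reading below 8th grade, an AUC of 0.79 (95% CI 0.72-0.87), sensitivity 0.80 and specificity 0.67.

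Recruitment and Retention says that Spanish-speaking Hispanics will come in part from "a pool of subjects who participated in prior studies and have given permission to contact them in future studies". Expected Outcomes says that "mediation analyses will allow an assessment of the mediating effect of health literacy on health disparities".

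**The concern.** A fair test of whether the device changes the scale needs two groups alike in everything but the device. Here one group is selected for low scores on a literacy screener and the other was not. The selection is on variables closely related to the scale being validated, and the REALM and SAHLSA serve both as the gate into the trial and as two of the three concurrent-validity criteria.

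If the plan is followed as written, a tablet version that works exactly like the full-size one would be expected to show a lower mean. It might also show a smaller spread, lower alpha and weaker correlations with the criteria. A reader could take these for faults of the tablet. The reverse inference is unsafe too: a difference test that fails to reject is weak evidence of sameness, and the article sets no margin for how close is close enough.

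**Working it through.** **The protocol's own figures.** With equal-variance normal scores, sensitivity 0.80 and specificity 0.67 imply AUC = Phi((0.842 + 0.440)/sqrt 2) = Phi(0.906) = 0.82, inside the stated interval of 0.72-0.87. The screening figures are therefore coherent. Specificity is the share of people reading at or above 8th grade who are correctly screened out, so the earlier data must contain such people. The tablet sample is the 432 randomized. No sample size, power or margin is stated for Hypothesis 2 itself.

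**Share of the earlier sample that would pass the screen.** With prevalence p of reading below 8th grade (not given), the share is q = 0.80p + 0.33(1 - p).
- p = 0.20: 0.160 + 0.264 = 0.42
- p = 0.35: 0.280 + 0.2145 = 0.49
- p = 0.50: 0.400 + 0.165 = 0.57

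I widen this to q = 0.40-0.70.

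**Effect of selection when the two versions are identical.** Assume a bivariate normal screener and scale with full-range correlation r, keeping the lowest fraction q. With c = Phi^-1(q) and L = phi(c)/q, the selected screener has mean -L and variance v = 1 - cL - L^2. Then, in full-range SD units:
- scale mean shift = -rL
- scale variance s^2 = 1 - r^2(1 - v)
- correlation with the screener r' = r sqrt(v)/s
- alpha' = 1 - (1 - alpha)/s^2

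Worked case, r = 0.70, q = 0.50: c = 0, L = 0.798, v = 0.363.
- Mean shift = -0.70 x 0.798 = -0.56 SD
- s = sqrt(1 - 0.49 x 0.637) = 0.83
- r' = 0.70 x 0.603/0.829 = 0.51
- alpha 0.80 becomes 1 - 0.20/0.688 = 0.71

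Over r = 0.5-0.8 and q = 0.40-0.70:

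| Quantity | Selection alone gives |
|---|---|
| Mean | falls 0.25-0.77 SD |
| SD | 0.75-0.93 of its earlier value |
| Alpha of 0.80 | 0.64-0.77 |
| Correlation of 0.70 (r fixed at 0.70) | 0.48-0.57 |

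**Would the mean difference be significant?** The earlier total is not given. The only count is more than 320 Spanish-speaking Hispanics, so I use 320 as a low stand-in. z = shift/sqrt(s^2/432 + 1/320).
- Smallest shift (r = 0.5, q = 0.70): 0.248/0.0717 = 3.5
- Largest shift (r = 0.8, q = 0.40): 0.773/0.0665 = 11.6

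At an assumed two-sided 5% level the smallest case already has power of about 0.93. For q = 0.42-0.57, power is at least 0.998.

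**How far this depends on normality.** I repeated the check by simulation with a left-skewed (reversed gamma) screener, the scale linear in it, r = 0.70 and q = 0.40-0.70.

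| Gamma shape | Mean falls (SD) | SD ratio | 0.70 becomes |
|---|---|---|---|
| 4 (mild skew) | 0.31-0.68 | 0.90-0.94 | 0.61-0.65 |
| 2 | 0.29-0.67 | 0.94-0.97 | 0.65-0.67 |
| 1 (strong skew) | 0.25-0.64 | 1.00 | 0.70 |

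The mean falls in every case. The loss of spread and correlation does not survive strong skew.

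**Hypothesis 5.** Assume a 0.5 SD gap in literacy between two equal groups and selection on a screener correlated 0.5-0.8 with literacy, q = 0.40-0.70. By simulation the gap among those enrolled is 0.28-0.44 SD, that is 13-44% smaller ((0.50 - 0.437)/0.50 to (0.50 - 0.282)/0.50).

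**The case against.** A reader might infer that selection will make the tablet look less valid and that Hypothesis 2 stands or falls on this comparison. The protocol supports neither. No score distributions are given, and with a strongly skewed screener the SD and correlations hardly move. The comparison is one strand among several, carries no pass/fail rule, and names no test for alpha. Correlations with the REALM and SAHLSA also apply within language, so tests on them would rest on fewer than 432 people.

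It can also be said that an article need not spell out the reference subset, and that the team could restrict the earlier data, since it has already applied the cut-off to them. That is possible, but the sentence as written points to the values from the earlier study and to difference tests, and says nothing of a subset, an adjustment or a margin.

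Sample overlap is possible, not stated. The re-contact pool is mentioned only for Spanish-speaking Hispanics, with no share given, so a failure of independence cannot be asserted.

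On Hypothesis 5, the calculation covers only the path from race to literacy. The protocol does not claim that its results hold at all literacy levels, and the trial targets low-literacy adults on purpose. What remains is a point about how the result is worded.

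None of this removes the confounding in the comparison of means.

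**Conclusion.** The concern holds for the comparison with the earlier study. As written, it cannot separate a device effect from selection on literacy. For an identical tablet version the expected fall in the mean is about 0.25-0.77 SD, with z of 3.5-11.6 for 432 against 320. This rests on an assumed scale-screener correlation of 0.5-0.8, the lowest 40-70% enrolled, bivariate normality, all 432 contributing tablet scores unaffected by the intervention, and 320 standing in for the unknown earlier total. The direction also holds under the skewed distributions tried.

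Lower SD, alpha and criterion correlations are possible but not certain: a correlation of 0.70 could become about 0.5 under normality or stay near 0.70 with strong skew. A non-significant result would not show that the versions match. The Hypothesis 5 point is secondary and concerns scope. This should be corrected before analysis; it does not affect the test of the intervention against control.

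**What to change.** Compute the reference mean, SD, alpha and correlations in the earlier dataset after applying the same REALM/SAHLSA cut-off. Match or adjust for language, age and race/ethnicity, and exclude anyone found to be in both studies. If the versions are equivalent, the expected difference due to selection on the cut-off is then zero. Replace the difference tests with differences and confidence intervals judged against equivalence limits fixed in advance, and say how alpha will be judged. In reporting Hypothesis 5, state that the mediation results apply to low-literacy adults, since selection on a proxy for the mediator is expected to shrink the race-to-literacy path.

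The cost is some re-analysis, a few sentences, and a smaller reference sample. If 42-57% of 320 earlier participants passed the screen, about 136-181 would remain. The 95% half-width for a mean difference would be 1.96 x sqrt(1/432 + 1/136) = 0.19 SD down to 1.96 x sqrt(1/432 + 1/181) = 0.17 SD, and less if the earlier total is larger. The equivalence limits should be chosen with that precision in mind.
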